### Collection of health professionals attitudinal data

As it is anticipated that cervical ripening at home may change the workload within the labour suites, midwives working in the Unit will be asked to take part in focus groups. (The use of focus groups have previously been found to be valuable in studying organisational change [33]). It is anticipated that around five focus groups, each of six midwives and lasting one hour will be needed. Staff will be recruited from those working in the obstetric unit at the PRM. Those expressing interest will be given an information sheet about the study and asked to complete a consent form. The topic guide for the focus group will be generated by the social science researcher. The purpose of the focus groups will be to discuss any perceived changes in ward throughput, management, and organisation. The focus groups will also ascertain whether staff perceive there are any benefits or disadvantages to women having outpatient pre-induction cervical ripening, and explore any other topics they believe to be important in relation to this issue.

### Statistical issues

#### Sample size calculation

Three hundred women will be recruited, of whom about 150 will be in the experimental and about 150 will be in the control (placebo) group. The primary outcome on which this study is powered is the time interval from hospital admission to delivery. In women undergoing induction of labour with Bishop scores 0–4 and 5–8, the mean (SD) induction to delivery intervals are 19.65 (10.75) hours and 15.17 (6.80) hours respectively ([name], data on file). With 150 women in each of the IMN and placebo groups (300 in total) the study has 96% power at a 5% level of significance to detect a difference in mean time from admission to delivery of 4 hours, assuming a common standard deviation of 9 hours, using a two sample two sided t-test.

Women's experience of induction of labour will be explored qualitatively and quantitatively. As in the PRIM study, we will ask women to indicate satisfaction with the ripening process on a visual analogue scale. Assuming similar results in the PRIM study (that those pretreated with IMN will give a mean (SD) score of satisfaction of 7.0 and those who have prostaglandins only as the active ripening agent will give a mean (SD) score of satisfaction of 5.8, with a common standard deviation of 3.0, the study has 93% power to detect a significant difference in satisfaction rates, given a sample size of 150 in each group. Statistical power of 90% or above (at the 5% significance level) is maintained if the number of evaluable patients in each group is 133 or greater.

### Loss to follow up

We do not anticipate any appreciable loss to follow up i.e. women failing to return usable data on the primary outcome.

### Failure to initiate on randomised study medication

Those women who go into spontaneous labour after recruitment, but before starting trial drug, and those women who withdraw from the study at this stage will (if they consent to continuing use of their data) be included in the primary analysis, but excluded from a subsequent secondary analysis.

Since the treatment is self administered, there may be sub-optimal delivery of the assigned treatment, which may lead to a dilution of the anticipated treatment effect. For example, if 1 in 8 (or 12.5%) of the IMN women failed to properly administer the dose, the 4 hour treatment difference would be reduced to 3 hrs and 30 minutes. The study would still have 93% power to detect such a difference, and 81% power if this proportion of women rose to 1 in 4 (or 25%).

## Statistical analysis ground rules

The primary endpoint of time from admission to delivery will be compared between the two groups using a two sample two sided t-test, and then adjusted for covariates that are pre-specified as important using a linear model. The analysis will be performed at the conclusion of the study. Analysis of secondary outcomes will be using t-tests (or Wilcoxon tests) or chi-squared tests as appropriate to the distribution of the data, again with adjustment for covariates using appropriate generalised linear models.

All statistical analyses will be fully specified in a Statistical Analysis Plan, which will be signed off before the treatment codes are broken. All primary analyses will be according to the intention to treat principle. No interim analyses will be performed, other than those requested by the Data Monitoring committee. The results of these interim analyses, and/or any other unblinded data will not be revealed to the investigators or the Trial Steering Committee until after the study is complete.

Analysis of the questionnaire data will be carried out using SPSS and analysis of variance. Interviews and focus groups will be coded and analysed using a computer package (ATLAS Ti) used to facilitate analysis of qualitative data for emergence of salient themes.

A prospective economic evaluation will be conducted alongside the randomised controlled trial to estimate the cost-effectiveness of outpatient cervical ripening with IMN prior to induction of labour. The cost differences between the two groups, the IMN and placebo groups, will be measured, valued and combined with the clinical effectiveness data from the trial. The economic evaluation will incorporate data from all subjects recruited into the trial. The valuation of all resource inputs will be consistent with the notion of opportunity cost.

The economic evaluation will be conducted from a health service perspective and will take two forms; (i) an overall cost analysis and (ii) an incremental cost-effectiveness analysis, which will be expressed in several forms, for example, incremental cost per operative delivery prevented [34]. All analyses will be conducted on the basis of intention to treat. Outcomes and costs for the experimental and control groups will be compared using relative risks and 95% confidence intervals for dichotomous variables, Mann-Whitney-U tests for ordinal variables, and Student's t-tests for interval variables where parametric assumptions are met. Fieller's theorem will be used to calculate 95% confidence intervals for incremental cost-effectiveness ratios [35]. In the absence of stochastic data for all variables, a series of multi-way sensitivity analyses will be undertaken to explore the implications of uncertainty on the base-case incremental cost-effectiveness ratios. In addition, cost-effectiveness acceptability curves will be constructed using the net benefits approach [36]. All analyses will be performed with a microcomputer using Statistical Package for the Social Sciences (SPSS) software, version 11.5.

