### Randomisation

Randomisation to IMN or placebo will be in the ratio 1:1, using randomised permuted blocks. The randomisation schedule will be generated by the Study Data Centre at the Centre for Healthcare Randomised Trials (CHaRT) at Aberdeen University. The randomisation schedule will be used by the Clinical Trials section of the pharmacy at the Western Infirmary, Glasgow, to make up treatment packs (either active or placebo) for each patient, each labelled with the relevant unique study number. Active and placebo treatments will otherwise appear identical, so that this will be a double blind study. A copy of the randomisation schedule will be held at the Clinical Trials Pharmacy at the Western Infirmary, and at CHaRT only. None of the investigators will have access to the schedule until completion of the study.

Within one hour after recruitment of each subject, the pack number for the subject will be allocated by phone call to the automated telephone randomisation service located at CHaRT in Aberdeen.

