### Collection of maternal satisfaction/acceptability data

Outcome iii, women's experience of induction of labour, will be drawn from two approaches. First, all women will be asked to complete a short questionnaire one hour before taking IMN using simple visual analogue scales for pain and anxiety. Baseline anxiety status will be assessed using the Eysenck anxiety scale. Women will be asked to note other symptoms and comments. We will ask women to complete further questionnaires after each 16 hour treatment period. Women will be given a stamped addressed envelope to send the completed forms to the social science researcher after delivery. All women will also be asked to complete a short follow-up questionnaire after delivery to ascertain satisfaction with cervical ripening, labour and delivery, pain scores and comments on the labour (e.g. duration). Women will be given the post delivery questionnaire at the hospital for completion, and asked to hand it in prior to discharge from hospital. In addition to the questionnaire strategies described above, a consecutive series of women recruited in the second year of the study will be approached for consent to being interviewed three weeks after delivery. We aim to interview 20 women in total. The interview will collect in-depth responses to the situation of women being at home during cervical ripening, including views on whether they felt in control of the situation, how easy it was to administer the tablet, whether they managed to administer the tablet at the prescribed intervals and any other positive or negative feelings.

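### The questionnaire analysis names analysis of variance with no baseline term, although pre-dose pain and anxiety are collected: an inexpensive gain in precision, not an error

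*Protocol article*

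**What the plan says.** The protocol article lists women's experience of induction of labour among its three primary outcomes (Outcomes, Primary).

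- **Data collected.** Under Collection of maternal satisfaction/acceptability data, all women are asked to "complete a short questionnaire one hour before taking IMN using simple visual analogue scales for pain and anxiety". Baseline anxiety is also measured on the Eysenck scale. Further questionnaires follow each 16-hour treatment period, and one after delivery covers satisfaction and pain.
- **Questionnaire method.** Statistical analysis ground rules gives one sentence on method: "Analysis of the questionnaire data will be carried out using SPSS and analysis of variance". It mentions neither baseline nor covariates.
- **Other outcomes, same section.** Time from admission to delivery is to be "compared between the two groups using a two sample two sided t-test, and then adjusted for covariates" in a linear model. Secondary outcomes are tested "again with adjustment for covariates using appropriate generalised linear models".
- **Deferral.** The section adds: "All statistical analyses will be fully specified in a Statistical Analysis Plan, which will be signed off before the treatment codes are broken". That plan is not available here.

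**The concern.** The trial asks women for pre-dose scores, yet the one method named for the follow-up scores does not say that they will be used. As written, a primary outcome has a less efficient stated method than the secondary outcomes, which do carry an adjustment clause.

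If the analysis follows the sentence literally, intervals for pain and anxiety are wider than they need be. A chance difference between arms in baseline pain or anxiety also stays in the point estimate. What is at stake is precision. Randomisation protects the unadjusted comparison from bias.

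**Working it through.** **1. The protocol's own power figures.** Inputs from Sample size calculation and Failure to initiate on randomised study medication: 150 per arm, two-sided 5% level, t-test; time SD 9 h, satisfaction SD 3.0. The noncentrality is difference / (SD × √(2/n)), and power comes from the noncentral t distribution.

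| Case | Stated | Recomputed |
|---|---|---|
| Time, 4 h | 96% | 97.0% |
| Time, 3.5 h (12.5% dilution) | 93% | 91.9% |
| Time, 3 h (25% dilution) | 81% | 82.1% |
| Satisfaction, 7.0 v 5.8 (1.2 points) | 93% | 93.2% |
| Satisfaction, 133 per arm | 90% | 90.2% |

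For satisfaction the noncentrality is 1.2 / (3 × √(2/150)) = 3.46. All figures agree within 2 points, so no stated power is wrong.

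**2. Gain for pain and anxiety.** Adjusting one follow-up score for one linear baseline with correlation r multiplies the variance by 1 − r². The equivalent sample size is 150 / (1 − r²). The protocol gives no r, so 0.3 to 0.6 is an assumption.

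| r | Variance left | Variance removed | Equivalent n per arm |
|---|---|---|---|
| 0.3 | 0.91 | 9% | 165 |
| 0.5 | 0.75 | 25% | 200 |
| 0.6 | 0.64 | 36% | 234 |

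Interval width scales with √(1 − r²), so it falls by about 5% (√0.91 = 0.954) to 20% (√0.64 = 0.80). At r = 0.1 only 1% of the variance is removed.

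**3. Gain for satisfaction.** There is no pre-dose satisfaction score. The available covariate is baseline anxiety, whose correlation with satisfaction is unknown and likely to be weaker. With SD = 3 × √(1 − r²), 150 per arm and the stated 1.2 points:

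- r = 0: 93.2%
- r = 0.1: 93.5%
- r = 0.3: 95.2%

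**4. Time, for comparison.** The sample size section gives mean (SD) intervals of 19.65 (10.75) h for Bishop 0-4 and 15.17 (6.80) h for Bishop 5-8. Let p be the share with Bishop 0-4 (not stated; assumed 0.3 to 0.9). The share of variance explained by the two bands is

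R² = p(1−p) × 4.48² / [p(1−p) × 4.48² + p × 10.75² + (1−p) × 6.80²].

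- p = 0.3: 4.21 / (4.21 + 67.04) = 5.9%
- p = 0.5: 5.02 / (5.02 + 80.90) = 5.8%
- p = 0.9: 1.81 / (1.81 + 108.63) = 1.6%

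At about 6% (r = 0.25) the SD falls from 9.0 to 8.71 h. Power at 4 h goes from 97.0% to 97.7%, and the 95% interval half-width from 2.04 to 1.97 h.

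**The case against.** The strongest reply is that omission of the baseline is inferred from silence. Analysis of variance is a broad family that can hold repeated measures and covariates, and full specification is deferred to a SAP that may already use the baseline. That stands as a reason to call this an improvement and not an error. It does not remove the point: the neighbouring sentences carry an adjustment clause and this one does not.

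A second reply is that not every woman will have a pre-dose score. Women who labour or withdraw before starting the tablets remain in the primary analysis if they consent to use of their data, and the pre-dose form is posted back only after delivery. This also stands. A baseline-adjusted model needs a missing-baseline rule, or it would drop women from the intention-to-treat set.

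Three stronger readings are tempting but unsupported:

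- **Precision is thrown away for time.** A reader might infer this because the t-test comes first. The same sentence goes on to a covariate-adjusted linear model, naming the covariates is ordinary SAP detail, and the Bishop bands explain only about 2% to 6% of variance.
- **Randomisation should be stratified by Bishop score.** The protocol states "Randomisation to IMN or placebo will be in the ratio 1:1, using randomised permuted blocks" and names no stratification factor. That is a valid design. Chance imbalance is already allowed for in the t-test's standard error, and the quoted upper band runs to 8 although eligibility stops at 6.
- **Satisfaction would gain a lot of power.** That requires giving it a correlation suited to like-for-like scores, although it has no baseline, or testing a difference smaller than the protocol's 1.2 points.

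**Conclusion.** The point holds as a low-cost efficiency gain, confined mainly to pain and anxiety. If their baseline correlation lies between 0.3 and 0.6, adjustment is worth the equivalent of 15 to 84 extra women per arm (165 − 150 and 234 − 150); if the correlation is near 0.1, it is worth almost nothing. For satisfaction the likely gain is about 0.3 to 2 points of power. For time it is under 1 point at 4 h, and the planned linear model can already deliver it.

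This rests on the assumed correlations, on a roughly linear relation with baseline, and on the later questionnaires repeating the anxiety scale, which the article does not spell out (it does say that pain is scored after delivery). Nothing here suggests bias or a wrong power figure.

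**What to change.** In the SAP, before the treatment codes are broken:

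- Analyse follow-up pain and anxiety with a repeated-measures model containing treatment, time and the woman's own pre-dose score. Where there is a single follow-up score, use ANCOVA.
- Analyse satisfaction with a linear model containing treatment and baseline anxiety.
- Keep women without a pre-dose score in the intention-to-treat analysis by a simple method such as imputing the mean baseline over both arms combined, or a missing indicator. Report the number missing by arm, because the forms come back after delivery.
- For time, at most add one sentence stating that the linear model including baseline Bishop score gives the lead estimate and the t-test is supportive.

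The cost is a few sentences and the missing-baseline rule. No new data, no change to randomisation and no change to the sample size are needed.

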**Methods/design:**

The aim of this study is to determine whether IMN self administered by women on an outpatient basis improves the process of induction of labour. Specifically, we hypothesise that the use of outpatient IMN will result in a shorter inpatient stay before delivery, decreased costs to the health service and greater maternal satisfaction with ripening and induction of labour, compared with placebo treatment.

In the study described here (the "IMOP" study), women scheduled for induction of labour at term, and who require pre-induction cervical ripening will be randomised to self-administer at home either IMN 40 mg, or a placebo, each vaginally, at 48 hours, 32 hours and 16 hours before scheduled hospital admission.

After admission to hospital, treatment will revert to the usual induction of labour protocol. We will compare the primary outcomes of the elapsed time interval from hospital admission to vaginal delivery, the costs to the health service of induction of labour, and women's experience of induction of labour in the two groups.

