There is increasing interest in outpatient cervical ripening. This interest is driven at least in part by financial costs associated with an inpatient stay in the labour ward. The estimated cost for 24 hour labour ward stay is £500 – £1000 [North Glasgow University Hospitals Trust Finance department – personal communication], thus a 30% reduction in the inpatient ripening phase of 12 hours would be associated with a cost saving of £75 – £150 per patient. Additionally, there is a wish to "deinstitutionalise" the process of labour, and, where appropriate, to offer women the opportunity to remain as an outpatient for a longer period of time. Hofmeyer notes that information on women's views on cervical ripening and induction of labour are conspicuously lacking [29]. A small number of studies, including Biem et al (2003) [5] and PRIM [11] have provided some pilot evidence that women report positive views about outpatient cervical ripening. Additionally, self administration of vaginal tablets on an outpatient basis is acceptable to women in other clinical situations [30]. There is as yet no research evidence on the views of women who have experienced IMN induced cervical ripening in an outpatient setting, and women's acceptance of the novel situation of "pre-induction cervical ripening induction at home" is vital to its ultimate success. IMOP will address not only the clinical efficacy of outpatient administration of IMN for pre-induction cervical ripening, but also the economics of this strategy together with an assessment of women's views and experiences.

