### Trial design

IMOP is a double blind, randomised, placebo controlled trial in a single clinical setting. Active and placebo treatment will be allocated in a 1:1 ratio. The primary outcome measures are the effect of outpatient pre-induction cervical ripening with IMN on:

i. The elapsed time from hospital admission to delivery (defined as the time from admission to inpatient induction or admission in labour to delivery – either vaginally or by caeserean section)

ii. The costs of induction of labour

iii. Women's experience of induction of labour (maternal satisfaction)

iv. Operative delivery rates

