### Recruitment and consent

Subjects will not be formally recruited to the study until the decision to induce labour is made. Potential subjects will be informed about the trial and given written information in the third trimester. Those women who wish to participate and who understand the nature of the trial will be asked to complete and sign two copies of the consent form. Those women who do not wish to participate, or who are ineligible will be asked (verbally) for permission to record some basic data so that the generalisability of the trial can be subsequently assessed.

Women scheduled for induction of labour at term will be recruited and randomised at an antenatal visit by the clinical research fellow, up to seven days prior to scheduled admission for induction of labour. A vaginal examination will not be repeated if one has been done and each of the components of the Bishop score documented within 7 days of anticipated start of outpatient treatment. Women willing to participate in the study will be given their randomised study medication (either IMN tablets or placebo) at this visit, with instructions to self-administer the tablets vaginally starting 48 hours prior to the scheduled time of admission for induction of labour.

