### Interventions

The intervention is one tablet inserted vaginally on three occasions every 16 hours. In the experimental (IMN) group, a 40 mg IMN tablet will be self-administered vaginally by the patient at home 48, 32 and 16 hours before scheduled admission for induction of labour. In the control group, a placebo tablet, with an identical appearance to that of IMN, will be self-administered vaginally by the patient at home 48, 32 and 16 hours before scheduled admission for induction of labour.

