## Collection of outcome data

### Clinical data

Outcomes i, and iv – xiii will be recorded by the attending midwifery staff and the clinical research fellow onto a dedicated Case Report Form which will be placed in the case notes of each participating subject. Data will be collected on the health service resources used in the treatment of each woman and infant during the period between randomisation and hospital discharge to determine outcome ii. The trial data collection forms will record the duration and intensity of maternal and neonatal care, based on standard criteria for level of care, as well as profile maternal and neonatal complications. The start of labour will be defined as the start of regular uterine contractions 3 in 10 (mild to moderate in intensity), with a cervical dilation equal to or greater than 3 cm. Compliance will be assessed, as far as possible, by asking subjects to complete a diary card indicating when they took study medication.

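### The IMN-minus-placebo cost difference leaves out any routine cost of delivering home ripening, so it cannot alone show that home IMN saves money against usual care

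*Protocol article*

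**What the plan says.** Cost to the health service is one of the primary outcomes (Outcomes, Primary). Under Statistical analysis ground rules, the economic evaluation is meant "to estimate the cost-effectiveness of outpatient cervical ripening with IMN prior to induction of labour". The section Why is a trial needed now? likewise promises to address the economics of the outpatient strategy. It projects that "a 30% reduction in the inpatient ripening phase of 12 hours would be associated with a cost saving of £75 – £150 per patient", from a ward cost of £500–£1000 per 24 hours. The abstract and the closing Discussion look ahead to wide adoption if the treatment works and is economical.

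The contrast is then fixed: "The cost differences between the two groups, the IMN and placebo groups, will be measured, valued and combined with the clinical effectiveness data from the" study. There are two arms and no usual-care arm: "Active and placebo treatment will be allocated in a 1:1 ratio" (Trial design).

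Both arms follow the same home pathway. Under Recruitment and consent, participating women "will be given their randomised study medication (either IMN tablets or placebo) at this visit, with instructions to self-administer the tablets vaginally". Under Interventions, "In the control group, a placebo tablet, with an identical appearance to that of IMN, will be self-administered vaginally by the patient at home", at the same three times as the IMN group.

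The costing covers "health service resources used in the treatment of each woman and infant during the period between randomisation and hospital discharge" (Clinical data).

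**The concern.** A service deciding whether to adopt home IMN would compare it with admission under its usual induction protocol and no home tablets. The trial compares home IMN with home placebo. Placebo is the right control for the drug's effect, but the placebo arm carries programme costs that usual care does not. Whatever it costs in routine practice to issue tablets, explain their use and carry out any examination needed only for home treatment falls on both arms and drops out of the difference.

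The resulting error has one direction. It can only flatter IMN when the trial difference is read as a saving against usual care. It matters because cost is a primary outcome and the projected saving per woman is modest, so delivery costs need not be large to take up a material share of it.

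**Working it through.** **Inputs from the protocol article**
- Ward cost: £500–£1000 per 24 hours; inpatient ripening phase 12 hours; projected reduction 30% (Why is a trial needed now?).
- Powered difference: 4 hours from admission to delivery (Sample size calculation).
- Routine delivery cost per woman, c: not given. The values below are illustrations, not estimates.

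**Step 1: reproduce the article's figure.**
- £500/24 × 12 × 0.30 = £75.
- £1000/24 × 12 × 0.30 = £150.

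This matches the stated £75–£150. The sum counts ward time only and deducts nothing for delivering home treatment.

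**Step 2: value the powered difference at the same rates.**
- £500/24 × 4 = £83.
- £1000/24 × 4 = £167.

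**Step 3: relate the trial contrast to usual care.** Let C_I, C_P and C_U be the mean cost per woman with home IMN, with home placebo, and with admission without home treatment. If placebo does not alter the inpatient course, and research-only costs are set aside, then C_P = C_U + c. Hence

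C_U − C_I = (C_P − C_I) − c.

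The saving against usual care is the trial saving less c.

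**Step 4: what cancels and what does not.**
- Cancels: dispensing, instruction, any examination made only for home treatment, and contacts prompted by tablet-taking itself in either arm.
- Stays: IMN drug cost (unless placebo tablets are costed as if they were IMN) and contacts, complications or admissions caused by IMN.

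**Step 5: net saving for assumed values of c.**

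| Assumed c | Projected saving, £75–£150 | 4-hour difference, £83–£167 |
|---|---|---|
| £10 | £65 to £140 | £73 to £157 |
| £25 | £50 to £125 | £58 to £142 |
| £50 | £25 to £100 | £33 to £117 |
| £75 | £0 to £75 | £8 to £92 |
| £100 | −£25 to £50 | −£17 to £67 |

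At c = £25 the overstatement is 33% of the £75 figure and 17% of the £150 figure. At c = £50 it is 67% and 33%.

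**Step 6: break-even.** This needs no assumption about c. The saving is gone at c = £75 (low ward cost) or £150 (high ward cost) on the projected saving, and at £83 or £167 on the 4-hour difference.

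**The case against.** The strongest reply is that the plan does not promise a saving against usual care. The abstract states the cost hypothesis as "decreased costs to the health service and greater maternal satisfaction with ripening and induction of labour, compared with placebo treatment", and read that way the randomised difference answers it. This stands: a conclusion confined to IMN versus placebo would be sound. The difficulty arises because the stated aim of the economic evaluation and the talk of adoption invite the wider reading.

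A second reply is that the details may lie elsewhere. Inputs are to be valued at opportunity cost, multi-way sensitivity analyses are planned, and a statistical analysis plan and a fuller protocol exist. These could value placebo-arm programme resources so that they do not cancel. That is possible, and it is why overstatement is conditional rather than established. But the contrast is fixed in the article, and nothing there mentions a comparator without home treatment.

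Third, c may be small. Recruitment takes place at an antenatal visit that is not described as additional, an examination documented within 7 days is not repeated, and no telephone advice service for participants is described. Consent, questionnaires and telephone randomisation are research costs that ought to cancel. All of this stands. It argues for measuring c, not for leaving it out.

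A reader might infer two stronger points that the documents do not support:
- **That IMN is charged for nothing beyond its tablets.** Staff time, complications and neonatal care are costed, and unscheduled admission is a compared outcome, so harms specific to IMN remain in the difference.
- **That issuing the tablets falls outside the costing window.** The pack is allocated after recruitment (Randomisation) and then handed over with instructions, so dispensing and instruction follow randomisation and are inside it.

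**Conclusion.** The concern holds in a limited form. The stated contrast isolates the cost effect of the drug given at home. It does not measure the cost of the home strategy against admission without home treatment. Read as the latter, it overstates the saving by c, for any c above zero.

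The size is unknown because the documents give no delivery cost. Only the break-even is firm: £75–£150 on the article's projected saving and £83–£167 on the powered difference. Both ranges rest on the quoted ward cost applying to every hour saved, and on placebo leaving the inpatient course unchanged.

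It would go too far to say that home IMN is likely to prove cost-neutral or dearer. At an assumed c of £60, for instance, the 4-hour saving is still £23–£107 (£83 − £60 and £167 − £60). Reversal needs a larger delivery cost or a smaller effect. A correction is still worth making, because the error has one direction and bears on a primary outcome.

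**What to change.** Keep the randomised IMN-minus-placebo cost difference and report it. Beside it, report a costed comparison that:
- charges each IMN woman the routine-practice cost of delivering home treatment (dispensing, instruction, and any examination made only for it), in addition to the drug;
- costs the placebo programme at zero;
- excludes research-only costs such as consent, questionnaires and telephone randomisation;
- states the break-even value of c.

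Base any claim that home IMN saves money against usual care on this second comparison. If it is not done, limit the cost conclusion to IMN versus placebo.

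The cost is a few extra unit costs, obtainable through the finance department questionnaire already planned under Collection of health cost data, plus some wording in the economic analysis. Randomisation, blinding, sample size and the efficacy analysis are unaffected. The downside is a slightly less favourable cost result for IMN in the added comparison.
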